## Abstract

**Background:**

Atrial fibrillation (AF) after radiotherapy (RT) in patients with breast cancer (BC) is a relatively new and understudied topic. AF can increase the risk of stroke and other serious cardiovascular complications, compromising patients’ quality of life and survival. Screening of AF, both asymptomatic and symptomatic forms, is therefore essential for optimal management.

**Objective:**

The aim of the Watch Your Heart After Radiotherapy for Breast Cancer (WATCH) study is to assess the incidence of AF (symptomatic or asymptomatic) occurring throughout a 5-year follow-up after RT and to investigate whether cardiac radiation exposure is associated with the occurrence of such events.

**Methods:**

WATCH is a cohort study that will include 200 patients over 65 years old, treated with RT for BC 5 years before inclusion and without a history of AF. Cross-sectional screening for AF at the time of the scheduled 5-year post-RT visit will be conducted by recording data from a Withings ScanWatch smartwatch for 1 month, confirmed by an electrocardiogram (ECG), and validated by a physician. In addition, a transthoracic echocardiography (TTE) will be performed, providing a comprehensive assessment of cardiac structures, and allowing us to investigate the underlying etiology and assess the risk of complications. Patients’ medical records will provide retrospective information about the timing and risk factors for the occurrence of AF and other arrhythmias and cardiac diseases during the 5 years following RT. The development of deep learning algorithms for autosegmentation analysis of potentially critical substructures for the occurrence of AF, including cardiac chambers, the sinoatrial node, the atrioventricular node, coronary arteries, and pulmonary veins (PVs), will produce dosimetry linked to previous RT treatment for all contoured structures.

**Results:**

Enrollment started in October 2023 and will continue until mid-2026 to include 200 patients, which will ensure an 80% statistical power to detect a significant difference in AF incidence around 15% for the group of patients moderately exposed (<75th percentile of the mean heart radiation dose) and 25% for the group of patients highly exposed (>75th percentile of the mean heart radiation dose). The results are expected by the end of 2026.

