### Sample Size Calculation

The calculation of the required sample size was conducted within the framework of an exploratory study. The required number of patients was set to 200 based on a statistical power of 80% with a type I error rate of 5% and theoretical percentages of AF incidence of 10% for the group of patients considered moderately exposed (<75th percentile of the average heart radiation dose distribution) and 25% for the group of patients considered highly exposed (>75th percentile of the average heart radiation dose distribution) [60]. We plan to include these 200 patients in approximately 30 months.

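### The Abstract claims 80% power for 15% vs 25% AF with 200 patients; the Methods use 10% vs 25%, and at the Abstract's rates power is about 37%

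*Protocol article*

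**What the plan says.** Two current parts of the protocol article describe the power for the primary comparison, which is AF occurrence over five years in patients below versus at or above the 75th percentile of whole-heart dose.

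- **Abstract, Results:** enrolling 200 patients is said to ensure "80% statistical power to detect a significant difference in AF incidence around 15% for the group of patients moderately exposed", set against "25% for the group of patients highly exposed".
- **Methods, Sample Size Calculation:** 200 patients at 80% power and a 5% type I error rate, with "theoretical percentages of AF incidence of 10% for the group of patients considered moderately exposed" and "25% for the group of patients considered highly exposed".

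Both parts define the exposure groups by the 75th percentile of mean heart dose. The Planned Statistical Analysis section makes every test two-sided at 5% and names the chi-square test for categorical variables.

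**The concern.** Sample size, power, the rate in the highly exposed group and the exposure cut are the same in both places. Only the rate in the moderately exposed group changes, from 10% to 15%, which shrinks the difference from 15 to 10 percentage points. One sample size cannot give 80% power for both.

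This is the headline power statement for the primary outcome, in the most widely read part of the article. A reader who trusts it would put the chance of missing a true 15% vs 25% difference at 20%. On the documented design that chance is about 62.5% (100 − 37.5). A null result could then be taken as fair evidence against a difference the study was unlikely to detect.

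**Working it through.** **Inputs**

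- N = 200 (Abstract; Sample Size Calculation).
- Groups split at the 75th percentile of heart dose (Abstract; Primary Outcome; Sample Size Calculation), so n₁ = 150 moderately exposed and n₂ = 50 highly exposed.
- Two-sided α = 0.05, z = 1.960 (Planned Statistical Analysis).
- p₂ = 0.25 in both places; p₁ = 0.15 (Abstract) or 0.10 (Sample Size Calculation).
- No loss to follow-up is applied, since none is stated.

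**Formula** (two proportions, pooled variance under the null)

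Power = Φ[(d − z·SE₀)/SE₁], where d = p₂ − p₁, SE₀ = √[p̄(1 − p̄)(1/n₁ + 1/n₂)] and SE₁ = √[p₁(1 − p₁)/n₁ + p₂(1 − p₂)/n₂].

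**Step 1: where the stated 200 and 80% come from.** Take the Methods rates, 10% vs 25%, with *equal* groups of 100:

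- p̄ = 0.175, SE₀ = √0.0028875 = 0.0537, SE₁ = √0.002775 = 0.0527.
- Power = Φ[(0.15 − 0.1053)/0.0527] = Φ(0.848) = 80.2%, and the required total is exactly 200.

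A one-sided test at 150/50 also comes close (80.8%; required total 196). The article states neither basis, so the equal-groups origin is an inference. Either way, the figure traces to 10% and not to 15%.

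**Step 2: the Abstract's rates on the documented design.** 15% vs 25%, 150/50, two-sided:

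- p̄ = (22.5 + 12.5)/200 = 0.175.
- SE₀ = √[0.175 × 0.825 × (1/150 + 1/50)] = √0.00385 = 0.0620.
- SE₁ = √[0.1275/150 + 0.1875/50] = √0.0046 = 0.0678.
- Power = Φ[(0.10 − 0.1216)/0.0678] = Φ(−0.319) = **37.5%**.

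**Step 3: other readings of 15% vs 25% with N = 200**

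| Split | Test | Power |
|---|---|---|
| 150/50 | two-sided, exact Pearson chi-square | 36.8% |
| 150/50 | two-sided, arcsine | 33.8% |
| 150/50 | two-sided, Fisher | 32.3% |
| 150/50 | two-sided, unpooled | 31.4% |
| 150/50 | two-sided, Yates | 29.9% |
| 100/100 | two-sided, pooled | 42.3% |
| 150/50 | one-sided 5%, pooled | 48.8% |
| 100/100 | one-sided 5%, pooled | 54.9% |

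None comes near 80%.

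**Step 4: what 80% would require at 15% vs 25%, two-sided**

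- At 3:1: n₁ = [1.960·√(4 × 0.144375) + 0.842·√(0.1275 + 3 × 0.1875)]² / 0.10² = (1.489 + 0.699)²/0.01 ≈ 479. With n₂ = 160 the total is 639.
- At 1:1: 250 per group, 500 in total.
- With 150/50 fixed and p₁ = 0.15, power reaches 80% only when p₂ is about 0.339.

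**Step 5: the Methods rates on the documented design.** 10% vs 25%, 150/50, two-sided:

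- p̄ = 0.1375, SE₀ = √0.0031625 = 0.0562, SE₁ = √0.00435 = 0.0660.
- Power = Φ[(0.15 − 0.1102)/0.0660] = Φ(0.603) = 72.7% (exact Pearson 73.5%).
- 80% would need 184 + 62 = 246 patients.

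Replacing 15% by 10% in the Abstract therefore removes the contradiction but does not by itself make the 80% correct.

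**The case against.** The strongest reply is that this is a slip in the Abstract and not a miscalculated design. The difference between the Methods rates, 25 − 10, is exactly 15 points, so the size of the difference may have been printed where the 10% rate belonged. Only the Sample Size Calculation section presents a calculation, and it uses 10%; nothing shows that the study was sized on 15%. On that view 37% describes a scenario the Methods never adopted, and the real shortfall is about 80% against 73%. The article also calls the study exploratory and lists the small sample among its limitations.

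Much of this is plausible. The slip is a reasonable guess, and the 639 patients and the 34% detectable rate matter only if 15% is really intended. But the sentence as printed gives 15% to the moderately exposed group and says the sample ensures 80% power, and that is false under every reading tried. The exploratory label and the limitations text do not make a specific power figure true. The slip reading also leaves the Abstract's 80% unsupported on the stated split and two-sided test.

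**Conclusion.** The concern holds. The Abstract and the Sample Size Calculation section contradict each other on the rate in the moderately exposed group, and the Abstract's power claim is wrong as written. On the documented design its true value is about 37%, so the stated 80% is too high by a factor of about 2.1 (80/37.5). That factor belongs to the 150/50, two-sided case. It falls to about 1.9 with equal groups (80/42.3) and 1.6 with a one-sided test at 150/50 (80/48.8), but the conclusion does not change.

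The result assumes that all 200 patients are evaluable, that the 75th percentile divides them 150/50, and that the comparison is an unadjusted test of two proportions. Which rate the team intends cannot be settled from the article.

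**What to change.** Rewrite the power sentence in the Abstract in one of two ways:

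- **If 10% is the planning rate:** give 10% vs 25%, as in the Sample Size Calculation section, and state the power for 150/50 with a two-sided 5% test, about 73%. Bring the 80% in the Sample Size Calculation section into line so the two places agree, and name the allocation and test used.
- **If 15% is now the expected rate:** use it in both places, state that power at 15% vs 25% is about 37%, and add that the contrast detectable with 80% power is 15% vs about 34%.

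The cost is a wording change to the rate and the power figure. It needs no extra patients and no change to eligibility, outcome, exposure cut or test. Analysis is not due to start until June 2026. The price is a less favourable stated power.

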**Conclusions:**

This study will contribute to generating new knowledge on AF after RT for BC and help considering the inclusion of AF screening into routine clinical practice for these patients. Identifying the dose-risk associations would improve RT delivery protocols to limit the occurrence of different forms of AF and, if necessary, initiate appropriate treatment.

**Trial Registration:**

ClinicalTrials.gov NCT06073509; clinicaltrials.gov/study/NCT06073509?id=NCT06073509&rank=1.

**International Registered Report Identifier (IRRID):**

DERR1-10.2196/67875

## Introduction

### Background

Breast cancer (BC) is the most common cancer in women [1]. Early screening and advances in treatment, including surgery, chemotherapy, hormone therapy, and targeted therapies, have significantly improved survival rates. Radiotherapy (RT) plays a crucial role in BC management by reducing the risk of local recurrence and improving overall survival, particularly following breast-conserving surgery [2]. Despite its efficacy, RT for BC can induce adverse effects on the heart, particularly when the heart is near the radiation field. Cardiac complications can include coronary artery disease, pericarditis, valvular heart disease, and myocardial infarction [3-5]. Emerging evidence also indicates a risk of atrial fibrillation (AF) in patients with BC that may manifest months to years after treatment [6,7]. AF is a common cardiac arrhythmia characterized by an irregular and often rapid heart rate [8,9] that can eventually lead to conditions with significant health impacts (stroke, heart failure, dementia) [10-12]. AF screening is challenging, further compounded by its frequent asymptomatic nature, which has often gone undetected in retrospective noninterventional studies. It is therefore crucial to further investigate the risk of AF in patients with BC as it may compromise the quality of life and survival of patients.

### Atrial Fibrillation in Patients With Breast Cancer

Cancer patients have an increased risk for developing AF, varying according to cancer type and stage [7] and medical treatments for cancer [13]. It has been suggested that patients with BC may also not be exempt from AF risk, but results between studies are conflicting. A recent study based on the Medicare database showed that the incidence of AF is significantly higher in patients following the year of the diagnosis of BC compared to a control population without cancer (3.3% vs 1.6%, *P*<.05) [6]. With longer follow-up, several retrospective studies have indicated higher AF rates in patients with BC compared to the noncancer population [14-21], but these results were not confirmed in a Danish cohort [22], a US case-control study [23], and a meta-analysis [19]. The impact of age could explain such discrepancies between studies, as illustrated in a large cohort study using the National Inpatient Sample database in the United States based on 40,030,380 adults’ hospitalization for cancer, where patients with BC aged >80 years had an increased risk of AF [24]. Similar results were observed in a systematic review and meta-analysis that found that older patients (age ≥65 years) with BC have a 4.5 times’ higher incidence of AF than younger patients with BC (8.6% vs 1.9%) [18]. Other important factors could impact the risk of AF in patients with BC, such as the medical treatments for cancer, including thoracic surgery, chemotherapy, endocrine therapy, or RT [25]. The effects of surgery and chemotherapy on AF risk have been widely studied, but few studies have documented the risk of AF after RT.

Indeed, some scarce studies have specifically analyzed the link between AF and RT for BC. In 2 studies, RT was associated with a significantly increased risk of AF when compared to a control population without cancer (relative risk [RR] 1.82, 95% CI 1.07-3.08) [26]; hazard ratio [HR] 1.25, 95% CI 1.05-1.48 [27]). However, in a US cohort study, the risk of AF was not significantly higher in patients treated with RT compared to the general population [28].

### Screening of Atrial Fibrillation: A Challenge

Most of the aforementioned studies were retrospective and based on medical records and hospitalization for identification of AF events and thus presented the limitation of potential undercapture of events, which is a concern for AF, as explained next.

AF is the most common arrhythmia, which affects 1% of the general population and about 10%-20% of individuals aged 80 years or more. The definitive method for diagnosing AF is through visual inspection of an electrocardiogram (ECG). Although an irregular pulse might suggest the possibility of AF, an ECG is essential to confirm the diagnosis. Although persistent AF is easily detected, other forms are hard to diagnose despite symptoms. This is due to the paroxysmal nature of many types of AF that might disappear on the way to the hospital for a 12-lead ECG evaluation. Holter monitoring might fail to detect paroxysmal AF if it does not occur on the day of examination. Moreover, AF may be asymptomatic [29], and the challenge in early screening of AF is compounded by its often asymptomatic nature, as approximately one-third of individuals with this form of arrhythmia are unaware of its presence [30]. This has led to the concept of silent AF, which describes subclinical, asymptomatic episodes of paroxysmal AF.

To overcome these limitations of 12-lead ECG and Holter monitoring, advancements in wearable technology have led to the development of smartwatches with integrated ECGs (30-second single-lead electrocardiogram [SL-ECG] recording), which allows continuous monitoring of cardiac activity and can help identify silent AF episodes that might be missed during a single evaluation [31-33]. The effectiveness and reliability of ECG smartwatches for the screening of AF has been demonstrated in several studies (sensitivity 55%-97.3%, specificity 60%-98.2% [31,34-36]), in particular for silent or paroxysmal AF, by measuring continuous cardiac frequency and SL-ECG [37-39]. Moreover, ECGs generated by smartwatches are considered effective and noninferior to ECG/composite 12-lead ECG/Holter/patch monitoring for AF screening [40,41], even if validation of the diagnosis through manual interpretation by a physician is required [39]. Regarding the adherence rate of smartwatch wearing in individuals over 65 years, the PulseWatch trial showed a decrease after 1 month (baseline: 73%; day 30: 63%; *P*<.05) [42], illustrating the limitations of a long period (>1 month) of follow-up with smartwatches in the frame of an AF-screening campaign.

Recently, the European Heart Rhythm Association published recommendations on the use of digital devices to detect and manage AF [43]. It concluded that systematic screening using intermittent ECGs may be beneficial to detect AF in individuals aged >65 years with comorbidities increasing the risk of stroke. RT has been shown to increase the risk of cardiovascular and cerebrovascular diseases [4,44] in patients with BC. It may thus be important to consider AF screening for patients who have undergone RT for BC, due to their increased risk of cardiovascular complications. The interest and feasibility of opportunistic screening for AF in women treated with RT for BC have never been investigated.

### Relationship Between Cardiac Exposure to Radiation and Atrial Fibrillation Among Patients With Breast Cancer

Women treated with RT for BC present clinical characteristics at baseline that may induce a higher risk of cardiac events independent of irradiation, and it is consequently crucial to consider cardiac dosimetry to better understand the potential association between RT and the occurrence of AF and then establish a causality link. The association between the mean heart radiation dose and AF risk have been poorly investigated. The Northern Ireland Cardiac Health Events After Radiotherapy (NI-HEART) Study of patients with lung cancer found a dose-response relationship with HR=1.75 (95% CI 1.03-2.97) [45]. For BC, a similar association with the mean heart radiation dose was observed, with HR=1.23 (95% CI 1.15-1.32) [46]. However, radiation exposure of the heart during RT is not homogeneous, and the mean heart radiation dose is often not relevant to evaluate cardiac substructure RT doses [47] that may be more relevant to evaluate associations with AF. Some studies have begun to explore the dosimetry of cardiac substructures, and recent data have demonstrated associations between cardiac substructure radiation doses and specific cardiac events or mortality in patients. In a cohort that included 238 patients with esophageal cancer treated with RT, increasing the mean left atrial radiation dose was associated with AF risk (with 30% for every 10 Gray increase) [48]. In the field of arrhythmias and conduction disorders, this was observed for the right atrium and the sinoatrial node and the risk of conduction disorders in patients with BC [49-51]. In the case of AF, the arrhythmogenic tissue is often located in the pulmonary veins (PVs), but these structures are not yet considered organs at risk during RT planning, despite a potential relevant association, as suggested in the NI-HEART Study, which investigated the PV radiation dose and the risk of AF in patients with lung cancer following RT. Dose metrics for both the left (V55) and the right (V10) PVs were associated with the incidence of new AF (HR 1.02, 95% CI 1.00-1.03, *P*=.005, and HR 1.01, 95% CI 1.00-1.02, *P*=.033, respectively) [52]. Further research is needed to accurately assess the radiation doses absorbed by some of these substructures and to determine whether the exposure of certain potentially critical structures can better predict the risk of cardiac arrhythmias, particularly AF, in patients with BC. Indeed, identifying critical substructures for AF in women undergoing RT for BC and demonstrating the dose-risk relationship could thus improve RT delivery protocols to limit the occurrence of these arrhythmias.

Manual contouring in radiation treatment planning is time-consuming, requiring meticulous effort to ensure precise delineation of volumes. In recent years, artificial intelligence (AI), particularly deep learning–based autosegmentation models, has emerged to mitigate this workload. These models are used for contouring organs at risk, offering significant improvements in consistency and efficiency, and substantially reducing the time required [53]. However, such deep learning autosegmentation models are scarce or inexistant for specific cardiac substructures, such as conduction nodes [54] or PVs [55], and remain to be developed.

### Study Rationale

Studies on AF and its potential link with RT for BC are relatively limited and have several limitations: the probable undercapture of AF events, particularly in the case of silent AF; the lack of details on the identification or diagnosis of AF; and the lack of precise dose metrics data for cardiac substructures.

In the population of patients with BC treated with RT, asymptomatic forms of AF are often missed in retrospective data collection, which typically identifies only symptomatic cases. Our study hypothesizes that at the time of the last follow-up visit (ie, 5 years post–breast RT by an oncologist), an opportunistic single-timepoint screening combining the use of a smartwatch and a cardiological evaluation, including an ECG and an echocardiogram, could help identify these asymptomatic cases. This would facilitate the management and potential treatment of these patients and increase the completeness of identifying incident cases potentially associated with RT.

Cardiac irradiation related to RT for BC can lead to an increased risk of cardiovascular diseases a few months to several years after treatment. However, precise data for AF, to establish a potential dose-response relationship, are sparse. Our study hypothesizes that the risk of AF could be associated with the radiation dose absorbed by critical cardiac substructures.

### Objectives

In this context and to explore these hypotheses, we will implement the Watch Your Heart After Radiotherapy for Breast Cancer (WATCH) cohort study combining a retrospective design and cross-sectional screening, which aims to investigate AF, including asymptomatic forms, that has occurred in patients with BC during 5 years following RT.

The *primary objective* of the study is to assess the incidence of symptomatic or asymptomatic AF occurring throughout a 5-year follow-up after RT and to identify nonradiation and radiation risk factors for the occurrence of such events.

The *secondary objectives* are as follows:

Perform a dosimetry evaluation of radiation doses absorbed in the heart and cardiac substructures (chambers, conduction nodes, coronary arteries, PVs) based on autosegmentation models developed with deep learning algorithms.Investigate whether the risk of AF is associated with cardiac irradiation characterized by these absorbed radiation doses.Assess the incidence of other arrythmias or cardiac diseases throughout the 5-year follow-up after RT and analyze these risks according to the level of cardiac irradiation.Evaluate the satisfaction and usability of the smartwatch with an integrated ECG in patients with BC.

## Methods

### Study Design

WATCH is a cohort study implemented as a retrospective and cross-sectional study [56] that will include female patients with left- and right-sided BC treated with postoperative RT after primary breast-conserving surgery. A cross-sectional collection at least 5 years after RT at the time of the last follow-up visit with the oncologist will be performed through smartwatch screening and a cardiology consultation (ECG and echocardiography) for AF screening. This 5-year post-RT timepoint for cross-sectional analysis has been chosen for 2 main reasons: first, to catch an opportunity of the last follow-up consultation with the oncologist to present the study to the patients and, second, a delay of 5 years post-RT appeared relevant to detect AF in patients with BC treated with RT, as observed in our previous work [49]. The retrospective collection of information will be based on questionnaires delivered to the patients to complete and checked against medical records. Figure 1 shows the study design.

